## Assignment of interventions: allocation

### Sequence generation {16a}

After the identification of patients through consultation of the outpatient database, the fulfillment of the inclusion criteria in the screening session and the patient’s agreement to participate in the study, a random sequence will be created using a random number allocation software, by a researcher external to the team involved in the execution of this study, in order to guarantee the concealment of the allocation of participants by the different groups. Randomization will be carried out in blocks with four strata and the eligible participants will be randomly assigned to three groups, in blocks of multiples of five, and will be stratified according to (i) age (50 to 65 years old; 66 to 80 years old) and (ii) MWD at the baseline (50 to 275 m; 276 to 500 m). The entire process will be overseen by a researcher who will not be directly involved in the intervention or assessments. This researcher will inform the research team of the final allocation of each participant.

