### Concealment mechanism {16b}

Participants will be grouped according to their demographic characteristics (age) and physical performance (walking ability) after screening assessment (time 0). Each participant will be assigned a random number, generated in a computer spreadsheet (Excel sheet). Then, randomization will be performed sequentially by three groups taking into account age and physical performance subgroups. To ensure that participants are assessed (initial screening) and randomized by their initial differentiating characteristics (age and physical performance), allocation concealment will be ensured until all baseline measurements are completed.

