### Implementation {16c}

The researchers (vascular surgeons and research assistants) will be responsible for the identification, selection, enrollment, and screening assessment of patients. Prior to the formal assessment, the data analyst will generate the allocation sequence and assign participants to groups. Other researchers will evaluate and implement the interventions (not blinded). The data analyst will analyze the data without uncovering the allocation of patients.

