## Assignment of interventions: blinding

### Who will be blinded {17a}

Participants will be blinded to the group they are assigned to; they will only know that all participants will receive a personalized and self-defined walking plan tailored to each one (a physical exercise prescription to be carried out in the area of residence). The researchers (vascular surgeons and research assistants) responsible for identifying, selecting, enrolling, and screening patients will be blinded to group assignments. A data analyst will generate the allocation sequence and assign participants to groups and will be responsible for data analysis. The researcher who will carry out the psychological intervention, the technician who will carry out the physical assessment, and the computer engineer who will define the route of the walking plan tailored to the patient, on the WalkingPad web platform, will not be blind as to the assignment group because each intervention has its specificity. Thus, this will be a single-blind study, as it will not be possible to blind the patients to the outcome or the researchers who implement and administer the intervention.

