### Procedure for unblinding if needed {17b}

The design is open-label with only outcome assessors and data analysts being blinded, so unblinding will not occur.

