### Data management {19}

Data will be entered as it is collected. The data collection forms—a set of questionnaires and the respective quotation for each item and total instrument score—will be transferred to the SPSS database. A member of the research team will enter the data and each time the database is closed will do a descriptive analysis of the data to ensure that the range of data values is correct in each variable. The data collection forms used, and their quotation will be available upon request from the principal investigator. Data will be analyzed by a data analyst who will be blinded to participant allocation. Questionnaires will be destroyed once the data is published.

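### The protocol claims blinded outcome assessors and a blinded analyst, but its own role descriptions leave the primary-outcome tester unblinded and give the analyst the allocation list

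*Protocol article*

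**What the plan says.** The protocol article describes blinding and allocation roles in several places.

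- **Procedure for unblinding {17b}:** "The design is open-label with only outcome assessors and data analysts being blinded, so unblinding will not occur".
- **Who will be blinded {17a}:** "the technician who will carry out the physical assessment" is listed with the psychological interventionist and the computer engineer as staff who "will not be blind as to the assignment group because each intervention has its specificity". On the analyst: "A data analyst will generate the allocation sequence and assign participants to groups and will be responsible for data analysis".
- **Implementation {16c}:** "Prior to the formal assessment, the data analyst will generate the allocation sequence and assign participants to groups". The section adds that the researchers who evaluate and intervene are not blinded, and that the analyst nevertheless works without uncovering the allocation.
- **Data management {19}:** "Data will be analyzed by a data analyst who will be blinded to participant allocation".
- **Sequence generation {16a}:** the sequence is created "by a researcher external to the team involved in the execution of this study".
- **Concealment mechanism {16b}:** "allocation concealment will be ensured until all baseline measurements are completed".
- **Trial design {8}:** the trial is labelled single-blind, with the patients as the blinded party.

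**The concern.** A reader of {17b} would credit the trial with a masked primary-outcome assessment and a masked analysis. The sections that say who does what describe the opposite on both counts.

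The endpoints make this important. Outcomes {12} defines pain-free walking distance by the onset of pain, functional walking distance by the patient's choice to stop, and maximal walking distance by pain that forces a stop. Table 1 also allows the treadmill test to end on voluntary exhaustion or fatigue. All of these can respond to cues from a tester who knows the arm. Patients know which tools they were given, so masking of the tester is one of the few protections left. For the analyst, knowing the arms removes the assurance that choices about models, exclusions and missing data were made without sight of which group benefits.

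**Working it through.** No arithmetic applies. The check sets the sections side by side.

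**Step 1: who measures the primary outcome?** Outcomes {12} measures the three walking distances by treadmill test and 6-minute walk test. Additional variables, in the same section, names those two tests as the source of the physical capacity data. Section {17a} gives the physical assessment to the technician. The technician is therefore the primary-outcome assessor.

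**Step 2: is that person blinded?**

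| Section | Status of the assessor |
|---|---|
| {17b} | blinded |
| {17a} | not blind |
| {16c} | those who evaluate are not blinded |

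The first row cannot be true together with the other two.

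**Step 3: is the analyst blinded?**

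| Section | Role or status of the analyst |
|---|---|
| {16c} | generates the sequence, assigns participants, analyses without uncovering allocation |
| {17a} | generates the sequence, assigns participants, analyses the data |
| {17b} and {19} | blinded |

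Whoever generates the list and assigns participants knows the allocation. Coded group labels would not mask that same person.

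**Step 4: does the external researcher in {16a} resolve this?** There are two cases.
- If that researcher is a different person, {16a} conflicts with {16c} and {17a} on who generates the sequence.
- If that researcher is the analyst, there is no conflict over generation, but the analyst holds the list and {19} cannot stand.

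Neither case makes all the sections true together.

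**Step 5: how could the arm reach the tester?** Section {16a} has each participant's final allocation reported to the research team. Eligibility criteria {10} lists a clinical physiologist technician in that team. Confidentiality {27} gives the whole team access to the exercise data on the app platform. Only the two experimental arms use the app, so having a platform record already separates them from the active control group.

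**Step 6: when is allocation known?** Recruitment {15} places the screening visit t0 before allocation. Section {16c} assigns groups ahead of a formal assessment that it does not define. Section {16b} conceals allocation until the baseline measurements are finished. These fit together if groups are assigned after t0, concealed through t1 and then disclosed. The order is not spelled out, so this needs clarifying; it is not a contradiction.

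**Step 7: what does patient blinding mean here?** Section {17a} says participants are told only that everyone receives a tailored walking plan. That is non-disclosure of the other arms, and it is compatible with holding a logbook or a phone. It still does not fit {17b}, which calls the design open-label and limits blinding to assessors and analysts.

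**The case against.** The strongest reply accepts the contradiction but limits what follows from it. Most of it stands.

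- **The technician may have a reason to know the arm.** A reader might infer from {17a} that the technician delivers no intervention and so need not know it. The documents do not establish this. Eligibility criteria {10} includes the technician in the team that implements the program, and {16c} speaks of researchers who both evaluate and intervene. Whether the technician can be masked is for the trial team to confirm.
- **Baseline need not be affected.** A reader might infer that t1 was measured by an unblinded tester after assignment. The safeguard in {16b} points the other way, and assigning is not the same act as disclosing.
- **Mitigations exist.** The treadmill protocol is standardized, and Table 1 rules out encouragement in both tests. These reduce tester influence. They do not govern every cue, or how pain onset is elicited and recorded.
- **Some of the risk lies with the patient.** The patient reports the pain and decides when to stop. Masking the technician would not remove bias from patients' own knowledge of what they received.
- **Masking cannot be restored backwards.** Trial status dates version 2.0 to 9 March 2022, with recruitment already under way and expected to finish on 30 April 2022. Where the technician already knows an arm, withholding the list changes nothing.

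None of this reconciles {17a} and {16c} with {17b}, or the analyst's allocation role with {19}.

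**Conclusion.** The point holds in limited form. The protocol states that outcome assessors and analysts are blinded, and the roles it assigns do not deliver either. This rests on the text alone, and confidence is high for both contradictions. They affect a property that readers will rely on when judging effort- and pain-dependent primary endpoints.

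The size of any resulting bias is unknown. It is tempting to express it in metres against the 20 m minimal clinically important difference under Statistical methods {20a}, but the documents offer nothing from which to derive such a shift, so none is given. The timing of allocation relative to t1 is an ambiguity, not a demonstrated bias. The patient-blinding label is loose, but it can be read as non-disclosure of the other arms.

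The conclusion assumes that the technician's physical assessment includes the two walking tests, as Outcomes {12} indicates, and that {16c} and {17a} mean what they say about the analyst.

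**What to change.** 1. **Tester.** For tests still to be done in patients whose arm the technician does not yet know, withhold both the allocation and the app-platform data from the technician. Ask patients not to reveal their arm or show the phone or logbook, and log any unmasking. Report all other tests as unblinded.
2. **Analyst.** Have someone other than the analyst generate and hold the sequence. The external researcher in {16a} can do this if that is a different person; otherwise another person is needed. Give the analyst arms coded A/B/C until the primary analysis is fixed. If the analyst already holds the list, withdraw the claim of a blinded analyst.
3. **Wording.** Reconcile {8}, {16a} to {16c}, {17a}, {17b} and {19} into one statement that gives each role's blinding status. State that single-blinding of patients means only non-disclosure of the other arms, and that allocation is disclosed only after the t1 measurements.

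The cost is modest: occasional unmasking to log, and an amendment submitted to the Ethics Committee as {25} requires. Possibly a separate list-holder is needed. Tests already done will carry a less favourable, but accurate, description of blinding.

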### Procedure for unblinding if needed {17b}

The design is open-label with only outcome assessors and data analysts being blinded, so unblinding will not occur.

## Data collection and management

### Plans for assessment and collection of outcomes {18a}

#### Data collection instruments for the primary outcome

The primary and secondary outcomes will be collected via self-report measures and through physical performance tests which are briefly described in Table 1. The timing of these measurements is shown in Fig. 2.

**Table 1 Tab1:** Summary of self-report primary and secondary outcomes, process, and screening variables, and respective assessment measures

Outcome	Measure	Brief description
Primary		
MWD PFWD FWD	*Treadmill test (TT)*	The treadmill test is an accepted method used in patients with IC to evaluate walking ability [34]. Performing a treadmill test before and after an intervention can provide an objective assessment of change in performance [35]. The modified Gardner-Skinner Treadmill Protocol will be used, where participants will begin to walk on the treadmill at 1 km/h with a 0% grade. After 2 min, the speed is increased to 1.6 km/h, at 0% grade. Then, the speed is increased by 0.8 km/h every 2 min until reaching 3.2 km/h. After reaching 3.2 km/h, the speed is kept constant, and the grade is increased by 2% every 2 min. The main difference between the modified protocol used and the original Gardner-Skinner Treadmill Protocol [36] is that the protocol used is better adapted to this study sample capabilities and equipment, since the original Gardner-Skinner Treadmill Protocol has a continuous speed of 3.2 km/h, and the grade is increased by 2% every 2 min. During the exercise, blood pressure and heart rate will be continuously monitored (Domyus Incline Rune, China). To implement the treadmill protocol, patients must be at rest, informed about the termination criteria (excluding safety criteria), about permission to use the handrail support, and informed about the claudication pain scale used [37]. The termination criterion is the limit of 500 m of pain-free walking distance (PFWD), but there are additional endpoints: voluntary exhaustion, fatigue and shortness of breath, and severe pain in another part of the body (e.g., spine). The claudication pain scale is a continuous scale from 0—indicating no pain, to 4—indicating severe pain, and patients are instructed to walk to near-maximal pain levels [37]. No encouragements will be given during the test. The test administrator has the necessary qualifications and is familiar with the protocol.
PFWD	*6-min walk test (6MWT)*	The 6MWT is a performance-based measure that evaluates the functional capacity of the individual to walk over a total of 6 min on a 100 ft (≈30 m) hallway, providing information regarding all the systems during physical activity [35]. The participants will be instructed to walk back and forth along the hallway to achieve the greatest distance possible. The participants will be allowed to stop and rest while the stopwatch continues to run. The American Thoracic Society guidelines will be used [38]. No encouragement through standardized verb phrases will be given because the aim is for the test to be as similar as possible to what happens in a real environment.
**Secondary outcomes**	**Measure**	**Brief description**
Physical and Mental Quality of Life	*Short-Form Health Survey (SF-36)*	This instrument consists of 36 items with different response scales assessing eight health concepts: limitations in physical activities because of health problems,limitations in social activities because of physical or emotional problems, limitations in usual role activities because of physical health problems, bodily pain, general mental health (psychological distress and well-being), limitations in usual role activities because of emotional problems, vitality (energy and fatigue), and general health perceptions. The SF-36 has been widely used in studies with this population and has excellent psychometrics [39, 40].
Vascular Disease-specific Quality of Life	*Vascular Disease-Specific Quality of Life Questionnaire (VAscuQoL-6)*	This is a specific measure of health-related QoL for patients with PAD, consisting of six items with different response scales [41, 42]. The total score ranges from 6 to 24, with higher results corresponding to a higer quality of life associated with arterial disease. The Brazilian-Portuguese version of the VascuQoL-6 presents adequate valid and reliable indicators allowing its use in patients with PAD with intermittent claudication symptoms [43].
Walking difficulties	*Walking Impairment Questionnaire (WIQ)*	This instrument assesses walking performance/abilities in three domains: distance (distances the individual can walk), speed (the speed the individual can walk), and stairs (number of stairs that the individual can climb without stopping), in a 5-point Likert scale (“none, slight, some, quite difficult, unable”). The distance comprises 7 items with a total score ranging from 0 to 28, with the highest results corresponding to a greater walked distance; speed has 4 items with a total score ranging from 0 to 16, with higher values indicating greater speed; stairs contain 3 items with a total score ranging from 0 to 12, with higher results indicating a greater ability to climb stairs [44]. The Brazilian-Portuguese version of the WIQ showed significant correlations between the WIQ domains and the SF-36 (functional capacity, physical aspects, bodily pain, and emotional aspects) and physical fitness performance (treadmill and strength tests). Intraclass coefficient correlation ranged from 0.72 to 0.81, and there were no differences in WIQ scores between the two questionnaire applications [45].
**Process variables**	**Measure**	**Brief description**
Illness representations	*Illness Perception Questionnaire - Brief (IPQ-B)*	This questionnaire contains 8 items assessing the cognitive and emotional representations of the disease in eight specific dimensions: consequences, timeline, personal control, treatment control, identity, concerns, understanding, and emotional representations [46, 47]. The response scale for each item ranges from 0 to 10 and higher scores indicate more threatening perceptions in each item/dimension concerning PAD. The Portuguese version showed good internal consistency [48]. This instrument has already been used in studies with this population.
Motivation stage for the change	*Stages of Change in Exercise Questionnaire (SCEQ)*	This questionnaire is composed of five items that represent each of the five stages of the Transtheoretical Model [49]. The Pre-Contemplation stage is characterized by the absence of intention to change behavior in the next 6 months (e.g., *I do not walk, and I do NOT intend to start walking in the next 6 months*). Contemplation is defined as the intention to change behavior within the next 6 months. When the individual intends to initiate behavior change within 1 month, the individual is classified as being in the Readiness to the Action stage. The Action stage is distinguished by having initiated a consistent and continued behavior change for 6 months or more and by moving the individual to the Maintenance stage. Subjects should indicate which item reflects their current exercise behavior in a dichotomous format of yes or no [50–52].
Locus of causality for exercise	*Locus of Causality for Exercise Scale (LCES)*	This scale comprises three items assessing the perceived choice (or autonomy) regarding performing physical exercise. Thus, this scale assesses the extent to which individuals feel that they freely choose to exercise (walking) rather than feeling that they have to for some reason, addressing the source of the initiation of behavior. An internal locus of causality is evident when an individual engages in a behavior freely and with no sense of coercion. The response scale on a 6-point Likert scale ranges from 1 to 6 and the total score ranges from 3 to 18. Higher scores indicate greater self-determination or a more internal perceived locus of causality [53]. The Portuguese version showed good internal consistency [54].
Planned behavior	*Questionnaire of Planned Behavior on PAD-Walking (QPBPW)*	This questionnaire assesses intentions, attitudes, subjective norms, perceived control, action, and coping plans regarding walking, in patients with PAD. The intentions scale is composed of 2 items with scores ranging from 2 to 10 points and higher scores indicating greater intention to perform the exercise (walking). The attitudes scale consists of 5 items, with scores ranging from 5 to 25 points and higher scores indicating a more positive attitude towards exercise. The subjective norms scale is composed of 3 items with scores ranging from 3 to 15 points, in which the higher the score, the higher is the perception of the importance attributed by other people to exercise. The perceived behavioral control scale evaluates the perception of control over-exercise, and it is composed of 4 items, with scores ranging from 4 to 20 points, and higher scores indicating a greater perceived behavioral control. The action and coping planning scale consist of 9 items, with scores ranging from 9 to 45 points, and higher scores indicating more action and coping plans regarding exercise (adapted for walking) [55]. The instrument has good internal consistency and was originally developed to be used with individuals with type 2 diabetes, and in this study, it was adapted to be used with patients with PAD, regarding walking.
Satisfaction of basic psychological needs	*Basic Psychological Needs in Exercise Scale (BPNES)*	This scale consists of 12 items and assesses the perception of satisfaction of the three basic psychological needs in the context of the exercise: autonomy, competence, and positive relationship (relatedness) on a 5-point Likert scale (“strongly disagree” to “strongly agree”). Scores range from 12 to 60 and higher scores indicate a greater perceived satisfaction of psychological needs during exercise [56, 57]. The Portuguese validation was performed on a sample of regular exercise participants and showed good psychometric properties in the three scales. For this study, the instructions were adapted to walking behavior.
Self-regulation in exercise	*Behavioral Regulation in Exercise Questionnaire (BREQ-3)*	This scale has 18 items, divided into six scales, assessing motivational regulations for exercise with a score ranging from 0 to 12 for each type of regulation on a 5-point Likert scale (“strongly disagree” to “strongly agree”). Higher scores indicate higher levels of one of the following types of behavioral regulation: amotivation, external, introjected, identified, integrated, and intrinsic [58–60]. The Portuguese validation was carried out on a sample of gym practitioners and showed good psychometric qualities in the six scales/types of motivation and regulation. For this study, the instructions were adapted to walking behavior.
**Screening measures**	**Measure**	**Brief description**
Sociodemographic and clinical data	*Sociodemographic and clinical data questionnaire*	It consists of information to be obtained directly from participants or clinical records: gender, age, living environment, marital and professional status, rural or urban areas of residence. Clinical data: clinical and surgical history, chronic medication, and lifestyle behaviors (alcohol and tobacco consumption, hours of sleep, and the number of daily meals).
Cognitive status	*Mini-Mental State Examination (MMSE)*	This is a widely used test of cognitive function, including tests of orientation, attention, memory, language, and visual-spatial skills. The total score ranges from 0 to 30, and higher results correspond to a better mental state. It will be applied at baseline as part of the screening assessment to ascertain exclusion criteria [61, 62].
Emotional status	*Geriatric Depression Scale-5 (GDS)* *Geriatric Anxiety Scale (GAS)*	As they are part of the screening, both questionnaires chosen to assess emotional state are very small, with dichotomous response scales, validated for a population over 65 years of age. Depressive symptoms are assessed through 5 items, with scores ranging from 0 to 5, and higher results corresponding to more depressive symptoms [63, 64]. A GDS-5 score ≥ 2 suggests clinical depression and the need for further evaluation. The Portuguese version has acceptable internal consistency. Anxiety symptoms are assessed through five items, with scores ranging from 0 to 5, and higher results corresponding to more anxiety symptoms [65, 66]. Portuguese internal consistency is high and a score ≥ 3 was optimal for the detection of DSM-IV Generalized Anxiety Disorder.
Physical activity	*International Physical Activity Questionnaire for elderly-Short Form (IPAQ-SF-E)*	The version adapted for the elderly was used, as individuals with PAD avoid physical activity due to claudicating pain and it is not expected to find patients practicing high levels of physical activity or regular physical exercise. This version, although validated for people over 65 years old, is smaller and the items are more adapted to the performance level of this sample. Thus, this version consists of 4 self-reported moderate-to-vigorous physical activity (MVPA) and sedentary behavior (sitting) items. The items encompass the following behaviors, in the last 7 days: the time spent sitting, the days and time spent walking, the days and time spent in moderate-intensity activities, and the days and time spent in vigorous-intensity activities. Scores range from 0 to indefinite minutes of physical activity per week and higher results correspond to a greater amount of physical activity performed. Results can be reported in categories (low, moderate, or high activity levels) or as a continuous variable (MET minutes per week). MET minutes represent the amount of energy expended carrying out physical activity [67–69]. The specificity of IPAQ-SF-E to identify low-active participants was 85%, and the sensitivity to identify the more active participants was 81%.
**Physical measures**	**Measure**	**Brief description**
**Physical measures**	*Ankle-brachial-index (ABI)*	Ankle Brachial Index (ABI) is the first low-cost diagnostic test for PAD [2]. The ABI is a simple and non-invasive test that will be obtained before and after the treadmill test by measuring the systolic pressures at the brachial artery, anterior tibial artery, and posterior tibial artery, in the supine position, in millimeters of mercury (mmHg), using a Doppler device. The ABI of each leg will be calculated by dividing the higher mean of three measures of the anterior tibial pressure or posterior tibial pressure by the higher mean of three measures of the right or left arm pressure (LifeDop 150 Doppler (8 MHz), USA).
**Hand strength**	*Hand grip strength (HGS)*	Hand grip strength (HGS) is a basic measure for determining musculoskeletal function, as well as weakness and disability [70]. The HGS produces an isometric strength measure that allows the identification of the muscular weakness of the upper limb and provides an indication of the overall strength since it reflects the strength of the lower limbs. Three consecutive measures of handgrip strength (in kilograms (kg)), at both hands, will be recorded in a standing position with the arms next to the body, elbow slightly flexed and wrist in a neutral position, through a hand-held dynamometer (Gripx EH101, China).
**Body composition**	*Body composition measures*	Weight (in kilograms), body mass index (kg/m^2^), body fat percentage (%), visceral fat level (%), skeletal muscle percentage (%), and resting metabolism (in kilocalories, kcal) will be measured through a bioimpedance scale (OMRON Body Composition Monitor BF511 (HBF-511 T-E/HBF-511B-E, Japan)). Height (in meters) will be measured using a tape measure.

